## Abstract

**Introduction:**

Breast cancer-related lymphedema (BCRL) is a serious and intractable complication that severely affects the quality of life and survival rates of cancer patients. Transcutaneous electrical acupoint stimulation (TEAS) has been applied in China for the treatment of lymphedema. However, there is currently no high-quality evidence-based data confirming the efficacy, safety, and preventive therapeutic role of TEAS for BCRL. This study aims to evaluate the efficacy and safety of TEAS pretreatment for BCRL through a multicenter, prospective, randomized, sham-controlled, parallel-group clinical trial, thereby providing evidence-based medical evidence.

**Methods and analysis:**

A total of 72 breast cancer participants scheduled for axillary lymph node dissection will be recruited from Yunnan Provincial Hospital of Traditional Chinese Medicine and the First Affiliated Hospital of Kunming Medical University. They will randomly assigned in a 1:1 ratio to the TEAS group or the Sham TEAS group, with 36 cases in each group. Treatment will be administered once daily from the first day before surgery to the third day after surgery (paused on the surgery day), and subsequently twice a week for 4 consecutive weeks, totaling 12 intervention sessions. This will be followed by an 18-month follow-up period. The primary outcome measures are the incidence and time of onset of lymphedema within 18-month postoperatively. Secondary outcome measures include: VAS scores for perceived swelling and lymphedema-related symptoms evaluated at baseline (T0), from preoperative to postoperative day 3 (T1-T4), upon completion of twice-weekly post-discharge treatments (T5-T12), and during monthly follow-ups until 18 months postoperatively (T13-T29); changes in circumference, edema stage, and severity of the affected limb evaluated at T0, before and after treatments from preoperative to postoperative day 3 (T1a/b-T4a/b), before and after twice-weekly post-discharge treatments (T5a/b-T12a/b), and at T29; skin thickness ultrasound and lymphangiography of the affected limb performed at T0, T2, T12, and T29; and serum inflammatory factor levels measured at T0, T4, and T12. Adverse events occurring during the trial will be recorded.

**Discussion:**

This study aims to evaluate the efficacy and safety of TEAS pretreatment for BCRL. If effective, TEAS will become a non-invasive adjunct therapy for preventing BCRL.

**Clinical trial registration:**

Chinese Clinical Trial Registry [website], identifier ChiCTR2400088117.

## Introduction

Breast cancer-related lymphedema (BCRL) is one of the relatively common complications following breast cancer surgery and falls under the category of “Edema” (Shuizhong) in Traditional Chinese Medicine (TCM). Its incidence rate can reach 6% to 63% (1, 2). Di Sipio et al. found that the probability of developing lymphedema in patients undergoing axillary lymph node dissection (ALND) is five times higher than in those undergoing Sentinel Lymph Node Biopsy (3). The incidence of BCRL following ALND is as high as 58.3% (4). The onset of lymphedema typically occurs between 3 months and 3 years postoperatively, peaking at 18 months. The incidence rate can reach 77% by 3 years postoperatively, followed by a small annual increase thereafter (5). Breast cancer patients who undergo ALND, sentinel lymph node biopsy, axillary radiation, and systemic chemotherapy face a lifelong risk of developing BCRL (6). Lymphedema is a chronic process; any factor causing obstruction or interruption of lymphatic drainage contributes to its occurrence (7). Since the treatment of breast cancer patients in China is predominantly based on comprehensive therapy involving modified radical mastectomy, chemotherapy, and radiotherapy, the incidence and severity of postoperative lymphedema are further exacerbated (8).

Currently, Western medical preventive measures mainly include preventive intermittent pneumatic compression (IPC) and preventive manual lymphatic drainage (MLD), limb rehabilitation exercises, and precautionary measures. These precautions include avoiding blood pressure measurement, blood draws, and injections on the affected upper limb; preventing burns, cuts, infections, and insect bites on the affected limb; avoiding saunas or hot baths; avoiding strenuous repetitive movements with resistance; and avoiding excessive fatigue or maintaining a fixed posture for prolonged periods (9). Preventive measures for BCRL are currently singular, and TCM involvement is primarily concentrated on treatment, with few reports on prevention. If patients miss the optimal window for conservative treatment and physiological lymphatic reconstruction, the condition may progress to a stage characterized by tissue proliferation, fat deposition, tissue fibrosis, and even ulceration or leakage, leaving surgery as the only option. However, current surgical interventions for BCRL involve high technical difficulty and long duration, and there is currently no ideal surgical procedure applicable to all patients with varying degrees of severity (10). Shifting the focus of BCRL management forward to the prevention stage allows patients to derive the maximum benefit. Therefore, actively exploring effective TCM preventive means to reduce the incidence of BCRL will not only break the limitation of singular preventive measures but also greatly benefit patients’ quality of life and promote the integrated development of Traditional Chinese and Western Medicine.

TCM has achieved significant clinical efficacy through its holistic concept and syndrome differentiation-based treatment (Bian Zheng Lun Zhi). It possesses unique advantages in treating edema; as early as the Inner Canon of the Yellow Emperor (Nei Jing), it was proposed that removing blood stasis through acupuncture and bloodletting could treat edema (11). Transcutaneous electrical acupoint stimulation (TEAS) is based on acupuncture but replaces needles with electrode pads, forming a current loop between two pairs of electrodes to stimulate acupoints, achieving effects identical to needle insertion (12). This therapy features controllable parameters, ease of standardized operation, and good reproducibility, and it can significantly save manpower costs associated with manual acupuncture manipulation. It allows for accurate regulation of stimulation intensity and can replace manual needle manipulation to save labor. As a novel therapy combining traditional acupuncture with modern electronic technology, TEAS has the advantages of being simple and non-invasive. Compared to manual acupuncture and electroacupuncture, TEAS does not require direct skin penetration, avoiding the risks of pain and infection, making it more easily accepted by patients. As a non-invasive treatment, it is also more readily accepted by surgical patients, and medical staff with basic training can operate it easily (13, 14). The physiological effects of TEAS are similar to those of electroacupuncture and manual acupuncture, capable of regulating the autonomic nervous system (15). Research by Jiang et al. indicated that electroacupuncture, TEAS, and manual acupuncture can all increase brain network connectivity, with TEAS showing superior effects (16). TEAS is widely applied clinically as a new acupuncture technology. Modern research also demonstrates that TEAS combined with other therapies has achieved significant efficacy in treating BCRL (17). Therefore, this study is designed as a clinical randomized controlled trial (RCT) to observe the preventive effect of TEAS pretreatment on patients undergoing ALND for breast cancer, aiming to provide new ideas and methods for the clinical prevention of BCRL.

## Methods and analysis

### Study design

This study is a multicenter, prospective, randomized, sham-controlled, parallel-group clinical trial designed to evaluate the efficacy and safety of TEAS pretreatment for lymphedema in patients undergoing ALND for breast cancer. A total of 72 eligible participants will be recruited and randomly assigned in a 1:1 ratio to either the TEAS group or the Sham TEAS group. The study protocol adheres to the Consolidated Standards of Reporting Trials (CONSORT) 2025 statement and the Standards for Reporting Interventions in Clinical Trials of Acupuncture (STRICTA) guidelines. The trial flow is illustrated in **Figure 1**, and the schedule for participant recruitment, interventions, and assessments is presented in **Figure 2**.

**Figure 1 f1:**
[figure not shown]
Trial flow diagram. TEAS, transcutaneous electrical acupoint stimulation; TNF-α, tumor necrosis factor-α; hs-CPR, high-sensitivity C-reactive protein; PCT, procalcitonin.

**Figure 2 f2:**
[figure not shown]
Schedule of enrolment, interventions and assessments.

### Recruitment and informed consent

From January 2025 to January 2026, patients meeting the inclusion criteria will be recruited and registered at the Department of Breast Surgery of Yunnan Provincial Hospital of Traditional Chinese Medicine and The First Affiliated Hospital of Kunming Medical University. Follow-up will continue until June 2027. After being informed about the study and its potential risks and benefits, patients will be required to provide written informed consent prior to randomization, followed by eligibility screening.

### Participants

#### Inclusion criteria

Patients meeting the aforementioned diagnostic criteria with clinical stage II or III breast cancer;Patients with invasive breast cancer and axillary lymph node metastasis confirmed by preoperative biopsy, who are scheduled to undergo axillary lymph node dissection (ALND);Absence of preoperative upper limb lymphedema;Female patients aged 18 to 75 years;Life expectancy ≥ 3 years as clinically estimated by a physician;Capable of self-care in daily life and able to cooperate to complete all interventions;Participation is completely voluntary; patients must sign the informed consent form and be willing to cooperate with follow-up during the study period.

#### Exclusion criteria

Upper limb edema caused by other diseases, such as edema of cardiac, renal, or nutritional origin.Patients currently using medications or undergoing other treatment regimens that conflict with this protocol.Patients with coagulation disorders, severe mental disorders, or severe cardiovascular, cerebrovascular, hepatic, or renal diseases.Physical disability of the affected limb, or a history of prior surgery or severe trauma on the affected limb.Women who are pregnant or lactating.

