Scheduled Treatment 2 Pre-treatment T6a	L												
	R												
Scheduled Treatment 2 Post-treatment T6b	L												
	R												
Scheduled Treatment 3 Pre-treatment T7a	L												
	R												
Scheduled Treatment 3 Post-treatment T7b	L												
	R												
Scheduled Treatment 4 Pre-treatment T8a	L												
	R												
Scheduled Treatment 4 Post-treatment T8b	L												
	R												
Scheduled Treatment 5 Pre-treatment T9a	L												
	R												
Scheduled Treatment 5 Post-treatment T9b	L												
	R												
Scheduled Treatment 6 Pre-treatment T10a	L												
	R												
Scheduled Treatment 6 Post-treatment T10b	L												
	R												
Scheduled Treatment 7 Pre-treatment T11a	L												
	R												
Scheduled Treatment 7 Post-treatment T11b	L												
	R												
Scheduled Treatment 8 Pre-treatment T12a	L												
	R												
Scheduled Treatment 8 Post-treatment T12b	L												
	R												
18 Months Postoperative (T29)	L												
	R												

Edema Staging:.

ISL Staging classifies lymphedema into 4 stages based on severity:

Stage 0: Latent or subclinical stage; no obvious limb swelling, no visible clinical symptoms.

Stage I: Obvious swelling with pitting edema; swelling subsides upon limb elevation.

Stage II: Swelling does not subside with elevation; early stage presents as pitting edema, while late stage becomes non-pitting due to subcutaneous fat deposition and fibrosis.

Stage III: Non-pitting edema with elephantiasis; skin thickening, roughness, folds, hyperpigmentation, loss of elasticity, and severe fibrosis.

Edema Severity:

Generally determined by comparing the circumference of the affected limb to the healthy limb at the same measurement point:

Mild edema: Circumference difference < 3 cm

Moderate edema: Circumference difference 3–5 cm

Severe edema: Circumference difference > 5 cm

Side of Affected Limb:

L, Left

R, Right

Measurement Instructions:

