The patient should be in a sitting or standing position with arms hanging naturally. Use a soft, non-elastic tape measure to encircle and measure the fixed points on both upper limbs. Measurement Points: Palmar crease, Wrist crease, 10 cm above wrist crease, Elbow crease, and 5 cm above elbow crease. Note: To avoid error, measure each point 3 times and calculate the average. Ensure measurements are taken at a fixed time, using the same tape measure, in the same position, and preferably by the same person to guarantee data accuracy and consistency.

Skin Thickness Ultrasound Examination: Changes in the skin thickness of the affected limb will be measured using ultra-high-frequency ultrasound. The specific measurement locations are detailed in **Table 5**. These assessments will be performed at baseline (T0), on postoperative day 1 (T2), after the 12th treatment (T12), and at 18 months postoperatively (T29).

**Table 5 T5:** Patient upper limb skin thickness record form.

Name: Age: Operated limb: Date of surgery:						
Measurement of skin thickness in the patient’s upper limbs						
Assessment timepoint	Measured limb	Measurement point 1	Measurement point 2	Measurement point 3	Measurement point 4	Measurement point 5
Baseline (T0)	L					
	R					
Postoperative Day 1 (T2)	L					
	R					
Scheduled Treatment 8 (T12)	L					
	R					
18 Months Postoperative (T29)	L					
	R					

Side of Affected Limb:.

L, Left

R, Right

Measurement points:

(a) Arm positioned in supinated position: 1. Medial upper arm. 2. Lateral upper arm measuring points are placed 7 cm above the cubital crease. 3. Medial forearm. 4. Lateral forearm measuring points are placed 7 cm below the cubital crease. (b) Arm in pronated position: 5. Mid-point dorsal hand surface measuring point is placed between the wrist and the first metacarpophalangeal joint.

Measurement Instructions:

In the initial measurement position, participants were seated with their upper arm slightly abducted, elbow fully extended, and hand in supination. For the fifth measurement, participants placed their hands in a pronated position on the dorsal side of the hand.

Lymphangiography of the Affected Limb: Lymphatic system imaging will be performed at baseline (T0), on postoperative day 1 (T2), after the 12th treatment (T12), and at 18 months postoperatively (T29).

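### The eligibility criteria do not secure a valid comparator arm for the secondary edema-severity grade

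*Protocol article*

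**What the plan says.** **Eligibility.** Under Exclusion criteria, the limb criterion reads "Physical disability of the affected limb, or a history of prior surgery or severe trauma on the affected limb". The opposite limb is not named. Inclusion criteria call for a scheduled axillary dissection without saying that it must be on one side only.

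Two criteria are not limited by side: "Absence of preoperative upper limb lymphedema" (Inclusion criteria) and "Upper limb edema caused by other diseases, such as edema of cardiac, renal, or nutritional origin" (Exclusion criteria).

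**Severity.** The notes to Table 4 say that severity is "Generally determined by comparing the circumference of the affected limb to the healthy limb at the same measurement point". The first band is "Mild edema: Circumference difference < 3 cm"; moderate is 3 to 5 cm and severe is above 5 cm. No subtraction of a preoperative difference is mentioned.

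**Measures that need no comparator.** ISL stage is clinical, for example "Stage I: Obvious swelling with pitting edema; swelling subsides upon limb elevation". The Secondary outcomes section also follows change in affected-limb circumference from baseline, skin thickness, lymphangiography and symptom scores.

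**Data collected.** The Table 4 instructions are to "encircle and measure the fixed points on both upper limbs", and the form has left and right rows from the preoperative visit onward.

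**Primary outcome.** It is the incidence and time of onset of lymphedema. The section gives no threshold and does not mention the between-arm difference.

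**The concern.** The severity grade needs two arms that can be relied on: one at risk and one stable reference. The criteria vouch for only the first. Three kinds of eligible participant have no such reference:

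- a woman having axillary dissection on both sides, who has no healthy arm;
- a woman with earlier axillary surgery or radiotherapy on the opposite side, whose opposite arm is not swollen at entry but may swell during the 18 months (the Introduction describes the risk after such treatment as lifelong);
- a woman whose opposite arm is wasted, deformed or enlarged by an old injury or operation, which gives a fixed offset.

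In the first two, swelling of the reference arm cancels swelling of the operated arm and the grade is too low. In the third, the grade is shifted up or down by a constant that has nothing to do with the surgery. The Removal criteria would not catch these women as mistaken inclusions, because they meet every published criterion. At stake is the validity of the severity comparison for these participants.

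**Working it through.** **1. The plan's own figure.** Sample size: 30 × 2 × (1 + 0.20) = 72, or 36 per group, as stated. The point does not depend on this figure; it only supplies the denominator in step 4.

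**2. The Table 4 bands with a swollen comparator.** Recorded difference = operated-arm swelling − opposite-arm swelling, for arms that were equal before surgery. The swelling values are illustrative.

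| Operated arm (cm) | Opposite arm (cm) | Recorded difference (cm) | Grade against an unswollen arm | Grade recorded |
|---|---|---|---|---|
| 4 | 0 | 4 | moderate | moderate |
| 4 | 2 | 2 | moderate | mild |
| 6 | 2 | 4 | severe | moderate |
| 6 | 4 | 2 | severe | mild |
| 4 | 4 | 0 | moderate | mild |

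Every row with a swollen comparator is graded at least one band too low.

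**3. A fixed offset, and what baseline correction does.** Corrected difference = current difference − preoperative difference.

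- Opposite arm 3 cm smaller before surgery, no swelling: raw difference 3 cm, in the moderate band before any operation. Corrected: 3 − 3 = 0 cm.
- Opposite arm 2 cm larger before surgery, operated arm swells 4 cm: raw difference 4 − 2 = 2 cm, mild. Corrected: 2 − (−2) = 4 cm, moderate.
- Equal arms before surgery, both swell 4 cm: raw 0 cm; corrected 0 − 0 = 0 cm, still mild. The operated arm's change from its own preoperative value is 4 cm.

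Baseline correction therefore repairs a stable offset. It does not repair bilateral dissection or an opposite arm that swells later. Those need an eligibility rule or own-arm change.

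**4. How many women.** The article gives no frequency, so the proportion p without a sound comparator is an assumption. Expected number = 72p; chance of at least one = 1 − (1 − p)^72.

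| Assumed p | Expected of 72 | Chance of at least one |
|---|---|---|
| 1% | 0.7 | 52% |
| 2% | 1.4 | 77% |
| 5% | 3.6 | 98% |
| 10% | 7.2 | >99.9% |

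For bilateral or previously treated opposite sides, downgrading also requires the opposite arm to swell. Take the article's own rates, about one-quarter (Discussion) and 58.3% after dissection (Introduction). The 2% to 5% range then becomes 1.44 × 0.25 = 0.4 to 3.6 × 0.583 = 2.1 women. Not all of these would cross a cut-off.

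**The case against.** **Only one outcome is exposed.** A reader might infer that these women's outcome cannot be graded validly at all. The article does not support that. ISL stage, change in the operated arm from baseline, skin thickness, lymphangiography and symptoms need no healthy arm. This stands and confines the point to the severity grade.

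**The primary outcome.** A reader might also infer that the errors enter primary incidence, where one woman is 1/36 = 2.8 percentage points of a group. The Primary outcome section does not tie incidence to the between-arm difference. The mild band has no lower limit, so a difference near 0 cm is not declared absence of disease, and a woman moved from moderate to mild remains a case. This also stands. The 2.8-point shift would follow only if the case definition, not shown in the article, used the between-arm difference.

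**Existing safeguards.** The two criteria without a side remove an opposite arm that is already edematous, and a stable old injury can be corrected from the preoperative measurements of both arms. That is right as far as it goes. But the article does not say that the correction is made, and neither safeguard covers bilateral surgery or later swelling of the opposite arm.

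**A condensed article of a one-sided design.** The forms carry a single field for the operated limb, and the diagnostic criteria that the Inclusion criteria refer to are not in the text. The full protocol may require unilateral surgery. That is possible and lowers the weight of the point. Still, the limb exclusion is published and expressly confined to one limb, so it is a stated rule of the wrong scope and not merely a detail left out.

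**No bias between groups is shown.** Eligibility is settled before allocation, so no systematic imbalance is expected. The harm is misclassification in a small trial.

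**Conclusion.** The point holds for the secondary severity grade. The published criteria admit women for whom the published rule gives the wrong severity, mostly too low, and the rule ignores any difference between the arms that existed before surgery.

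The grading errors in steps 2 and 3 follow from the article's own bands, with illustrative swelling values. The number of women rests wholly on an assumed frequency. At 2% to 5% it is 1.4 to 3.6 of 72 without a sound comparator, and about 0.4 to 2.1 whose opposite arm would also swell. The overall effect is therefore probably small. Nothing in the article shows that primary incidence is affected. The change is worth making because it is cheap and recruitment was at an early stage when the article was written.

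**What to change.** 1. **Eligibility.** Add an exclusion for planned bilateral axillary surgery and for prior axillary surgery or axillary radiotherapy on the opposite side. Do not extend it to trivial old procedures of the opposite arm: step 3 shows that a stable offset can be corrected, and a wider rule would cost recruits for no gain.
2. **Grading.** Define severity on the between-arm difference at each point minus its preoperative value at the same point. The Table 4 form already collects both arms before surgery.
3. **Participants already enrolled.** Check them against the new line. Keep anyone without a valid comparator in the randomised analysis and assess her on the operated arm's change from its own preoperative value. State that she is not to be taken out as a mistaken inclusion under the Removal criteria, since she met the criteria in force at entry.
4. **Primary outcome.** If the full case definition uses the between-arm difference, apply items 2 and 3 to it as well.

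**Cost.** One amended criterion, a few more screen failures and slightly more analysis work; no new measurement. Trial status reports 10 enrolled as of July 2025, so 72 − 10 = 62 of the planned participants were still to be recruited at that date.

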### Removal criteria

Cases that were mistakenly included and do not meet the inclusion criteria.

Patients who receive other treatments during the study period (e.g., surgical treatments for breast cancer-related lymphedema, including lymphaticovenular anastomosis [LVA], debulking surgery, vascularized lymph node transfer [VLNT], or liposuction).Patients with poor compliance or an insufficient observation period.Patients with incomplete study data.Patients who are lost to follow-up.Patients who experience severe adverse events during the study period, or are diagnosed with other major diseases, tumor recurrence, or metastasis, rendering the study protocol no longer applicable.

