### Data analysis

Software and Data Handling: All statistical analyses will be performed by an independent statistician using SPSS 25.0 software (IBM, Armonk, NY). Missing data will be imputed using the Last Observation Carried Forward (LOCF) method.

Normality and Continuous Variables: Measurement data will be assessed for normality using the Shapiro-Wilk (S-K) test. Data conforming to a normal distribution will be expressed as mean ± standard deviation (SD). Intra-group comparisons (pre- and post-treatment) will be analyzed using the paired samples t-test, while inter-group comparisons will be performed using the independent samples t-test. Measurement data that does not follow a normal distribution will be analyzed using non-parametric rank-sum tests.

Categorical Variables and Significance: Enumeration data (categorical data) will be presented as percentages or constituent ratios, and differences between groups will be analyzed using the Chi-square (χ²) test. All statistical tests will be two-sided, with the significance level set at αt 0.05. A P-value < 0.05 will be considered statistically significant.

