### Data collection and management

All data will be initially recorded in Case Report Forms (CRFs) and subsequently entered into the study’s data management system by the researchers. Relevant patient characteristics, such as names, ID numbers, and telephone numbers, will be recorded in an anonymized format. For participants who discontinue treatment or deviate from the protocol, researchers will make every effort to supplement missing outcome data during the follow-up phase. The database will be locked after the last participant has completed the final follow-up and the data has been verified by two personnel; once locked, no modifications can be made. All participant files will be encrypted, stored, and centrally managed by the research center with strict confidentiality to ensure data security and traceability.

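### The removal criteria take out randomised participants for reasons arising after randomisation, including surgery for the primary outcome itself, which understates incidence and leaves the arm comparison open to bias

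*Protocol article*

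**What the plan says.** The Removal criteria section of the protocol article lists who is to be taken out. Apart from mistaken inclusion, every reason arises during the study:

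- "Patients who receive other treatments during the study period (e.g., surgical treatments for breast cancer-related lymphedema", with four kinds of lymphedema surgery named as examples;
- "Patients with poor compliance or an insufficient observation period";
- "Patients with incomplete study data";
- "Patients who are lost to follow-up";
- "Patients who experience severe adverse events during the study period, or are diagnosed with other major diseases, tumor recurrence, or metastasis", where these make the protocol no longer applicable.

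The primary outcome is the incidence and time of onset of lymphedema up to the end of follow-up at 18 months. The Inclusion criteria require that no upper limb lymphedema is present before surgery.

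Two other sections point the other way. Data analysis states: "Missing data will be imputed using the Last Observation Carried Forward (LOCF) method". Data collection and management states: "For participants who discontinue treatment or deviate from the protocol, researchers will make every effort to supplement missing outcome data during the follow-up phase". The article has no intention-to-treat statement, and group differences in categorical data are tested by chi-square.

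**The concern.** A participant who enters without lymphedema and is later operated on for it has had the primary event. Removing her takes a known event out of the numerator and the denominator. The clause is also open-ended: surgery is only the example under other treatments, so a case treated in another way could fall under it too.

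The remaining reasons are not events in themselves, but they too are known only after randomisation. Compliance and adverse-event removals could differ between an arm stimulated at the highest tolerated intensity and an arm whose current falls to zero within 45 seconds. If they do, the participants left are no longer the groups that randomisation formed, and the result no longer estimates the effect of being assigned to TEAS.

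The article's rules also cannot all govern one analysis. Participants with incomplete data or lost to follow-up cannot be both removed and imputed. Seeking the outcomes of deviators has little use if they are then removed.

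**Working it through.** **Inputs from the article.** 30 per group before dropout, 20% dropout, 36 per group enrolled (Sample size calculation). Incidence after axillary dissection as high as 58.3%, with no time horizon stated (Introduction), and about one-quarter (Discussion). The article gives no removal shares, so every value of r below is an assumption.

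**Plan's own figure.** 30 × 2 × 1.20 = 72, or 36 per group, which reproduces. The design expects about 30 of 36 per arm to remain, so about 6 of 36 (17%) may go.

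**Incidence after removing a share r of events.** Observed incidence = p(1 − r)/(1 − pr).

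| r | p = 58.3% | p = 25% |
|---|---|---|
| 10% | 55.7% | 23.1% |
| 20% | 52.8% | 21.1% |
| 30% | 49.5% | 18.9% |

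For example, 0.583 × 0.8/(1 − 0.1166) = 0.528.

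**Equal removal, no true effect.** With 20% of events removed in each arm, both arms read 52.8% (or 21.1%). Incidence is too low, but there is no false difference. The simulated two-sided error of the chi-square test with 36 randomised per arm is about 5.2%.

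**Unequal removal, no true effect.** With 30% of events removed in the TEAS arm and 10% in the sham arm:

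- p = 58.3%: a false difference of about 6.3 points in favour of TEAS, simulated error 8.0%;
- p = 25%: 18.9% against 23.1%, a false difference of 4.2 points, simulated error 7.0%.

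Reversing the shares reverses the sign. With nothing removed, the simulated error is nominal (4.8% and 4.9%).

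**True effect present.** Suppose sham 25%, TEAS 12.5% (assumed), and 20% of events removed in each arm. Sham reads 21.1% and TEAS reads 0.125 × 0.8/(1 − 0.025) = 10.3%. The difference shrinks from 12.5 to 10.8 points. So the surgery clause tends to hide benefit when TEAS works.

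**Single cases.** Removing k cases from n shifts an arm by k(1 − p)/(n − k). With n = 30:

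- p = 58.3%: 0.417/29 = 1.4 points for one case, 0.834/28 = 3.0 for two;
- p = 25%: 0.75/29 = 2.6 points for one case, 1.50/28 = 5.4 for two.

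**Outer bounds for one arm with 6 of 36 removed.** At 21/36 events, the result lies between 15/30 = 50% (all six are events) and 21/30 = 70% (none is). At 9/36, it lies between 3/30 = 10% and 9/30 = 30%.

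**Why LOCF does not repair this.** Circumference and staging are measured through T12, about one month after surgery, and then only at T29. The article puts typical onset at 3 months to 3 years. For someone lost in between, the last staged observation will usually be free of lymphedema, so carrying it forward would code most such participants as event-free.

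**The case against.** The article never says in so many words that these participants leave the analysis, and analysis sets are commonly defined in a statistical analysis plan, which is not shown. LOCF could be meant only for missed visits among the 29 post-baseline time points. This softens the conflict but does not remove it. Incomplete data and mistaken inclusion make little sense as grounds for anything but exclusion from analysis. An analysis plan that kept everyone would contradict the stated rule.

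Several stronger readings are tempting and are not supported:

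- *The comparison is biased, and towards TEAS.* Bias in the comparison depends on how removals differ by arm. Participants, assessors and all researchers other than the acupuncturists are to be blinded, so with no true effect there is no stated reason for lymphedema surgery to fall in one arm. If TEAS works, the surgery clause would tend to shrink the apparent benefit. Removals for compliance or adverse events could act in either direction.
- *Many events will be lost to surgery.* The article describes such surgery as following late progression and as hard to apply widely. Removal shares of 10% to 30% are illustrations, not forecasts.
- *58.3% is the expected 18-month incidence.* The article does not say so, and its Discussion gives about one-quarter.
- *Each removed case moves an arm by 1/30.* That would be reclassifying a case. Removal also reduces the denominator, so the shift is smaller.
- *The worst safety outcomes vanish.* Safety evaluation provides for recording all adverse events, including whether they led to withdrawal, and for summarising them at the end. The problem lies in the efficacy comparison.

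**Conclusion.** The point holds as a defect in a stated rule, not as a missing detail. The removal list deletes primary events, so it understates incidence, and it leaves the randomised comparison open to bias whenever removals differ by arm. It also conflicts with two other stated rules. The size cannot be known from the article. Under the assumed shares, incidence is understated by 5.5 points (from 58.3%) or 3.9 points (from 25%) when 20% of events go. A 30% against 10% imbalance under no effect gives a false difference of about 6.3 or 4.2 points. Those shares assume that only events are removed. Neither the direction nor the presence of a false difference in this trial can be asserted in advance.

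**What to change.** Change the protocol wording, and align the analysis plan with it:

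1. The primary analysis includes all randomised participants in their assigned arm.
2. Lymphedema that leads to surgery or other lymphedema treatment counts as an event at its diagnosis date.
3. Non-compliers and participants with adverse events stay in the efficacy analysis.
4. Participants lost without an event are censored in the time-to-onset analysis, with a sensitivity analysis for incidence. They are neither deleted nor carried forward by LOCF.
5. The present list defines only a secondary per-protocol set.
6. Removal criteria, Data analysis, and Data collection and management are reconciled.

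This concerns who is analysed, not when treatment should stop. The cost is wording, plus a small dilution of the estimate by non-compliance. With 10 participants enrolled as of July 2025 and follow-up planned to June 2027, the article's timetable leaves room to make the change before outcomes are analysed.
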